### Randomisation

The randomisation unit will be the healthcare centres.

An independent statistician will carry out the randomised allocation to form groups of the same size from a list of the participating healthcare centres.

Posteriorly, within each unit, the mother-infant pairs will be selected by consecutive sampling, until the number is reached to form the cluster. Figure 1 describes how the pairs are recruited. During the consultations, the mothers will be informed about the study and asked if they would like to participate. All mothers that would like to have to sign a consent form and it will be confirmed that they meet all inclusion/exclusion criteria.

**Fig. 1 Fig1:**
[figure not shown]
Project structure

### Masking

In a study of this type it is impossible to mask the intervention. The analysis data will be performed by independent professionals blinded to the allocation group.

### Intervention

The healthcare professionals will carry out the recruitment, they will collect the study variables, apply the assigned intervention and perform all follow-up (consultation and/or telephone). Each one of them will only carry out one type of intervention: experimental or control. To avoid the differences in the measurement of variables and the application of the intervention as much as possible, previous training will be executed.

The organization and functioning of the health services will not be altered significantly to carry out the study, as the control intervention is the habitual practice and the intervention for the treatment group will be planned and conducted just like any other educational group intervention in the core of the primary healthcare team. The Working Plan is shown in Table 1.

**Table 1 Tab1:** Project Working Plan

Visit	Randomisation:2 months before visit 1	Trainig: 1–2 months before visit 1	Visit 1: < 1 month after birth	Visit 2: 2 months after birth	Visit 3: 3 months after birth	Visit 4: 4 months after birth	Visit 5: 5 months after birth	Visit 6: 6 months after birth
Study procedure***s***								
Randomisation	**X**							
Professional training		**X**						
Informed consent			**X**					
Recruitment			**X**					
Demographics			**X**					
Telephone contact				**X**	**X**	**X**	**X**	**X**
Interventions								
Standard practice				**X**		**X**		**X**
PROLACT intervention			**X**		**X**		**X**	
Outcomes measures								
EBF			**X**	**X**	**X**	**X**	**X**	**X**
PBF			**X**	**X**	**X**	**X**	**X**	**X**
CF			**X**	**X**	**X**	**X**	**X**	**X**
Reasons for abandoning breastfeeding			**X**	**X**	**X**	**X**	**X**	**X**
Acceptability of intervention			**X**					
Adherence			**X**		**X**		**X**	
Satisfaction							**X**	

The Standardized Services Portfolio for Primary Healthcare of the Community of Madrid defines four services of assistance to the supervision and development of the infant population. These services are the promotion of health habits, monitoring of development, systemic vaccinations and early detection of childhood problems.

These services are carried out transversally throughout the scheduled revisions [available at http://www.madrid.org/cs/Satellite?c=CM_Publicaciones_FA&cid=1142521116585&idConsejeria=1109266187266&idListConsj=1109265444710&idPagina=1343067104390&language=es&pagename=ComunidadMadrid%2FEstru].

#### Control group (usual care)

Usual care includes individual counselling about the benefits of maintenance exclusive breast-feeding during the first six months of the baby and about the introduction of complementary food after that. The mother should attend to the PHC at least twice, once before six months of age and another between six and 12 months of age.

#### Intervention group (educational group intervention)

This is an educational group intervention based on the workshop on breast-feeding designed by the expert group of the General Directorate of Primary Healthcare of the Madrid Health Department. It is structured in six weekly sessions of 120 min each. Its objectives are the acquisition, reinforcement and/or consolidation of the necessary knowledge and skills to initiate and maintain EBF as the newborns feeding, as well as the development of a positive attitude regarding breast-feeding. It consists of theoretical and practical content with the active participation of the mothers in the discussion group and the learning of skills through the direct practice of breast-feeding.

The activities will begin around the first month of life of the child (the maximum peak of abandonment according to existing studies) [20–22, 24] and it will take six weeks.

The mothers will be offered during the training session the possibility to come with the person that most influences their decision to breast-feed (social support) [15, 17].

Follow-up will be conducted through regular revisions according to the protocol and telephone calls to collect the study variables.

### Variables

#### Outcome variables

The main outcome variable is the percentage of infants who continue exclusively breastfed at six months.

The secondary outcome variables will be:Type of feeding at six months (categorical: EBF, PBF, CF).Duration of EBF (days) = (Date of abandonment EBF – Date of birth of infant).Reasons for abandonment of BF (semi-structured questionnaire created for the study).Number of group education sessions to which the dyad attends. Adequate adherence is considered as attendance to at least 85% of the planned sessions.Degree of satisfaction with the educational group intervention (measurement instrument: SERVQUAL).

The prognostic variables will be:For the professional: age (years), sex, breastfeeding training received.For the mother: age (years); education level (low – primary studies only; medium - high school completed, technical training or other non-university studies completed; high - university level education completed); income level; nationality; working situation of the mother (if she works outside the home and the number of hours per working day/ days per week); living situation with partner; obstetric history (pregnancies/abortions/live births); type of birth (vaginal/caesarean; single/multiple); Previous breastfeeding experience; peso(kg); size(cm); smoker (yes/no).For the newborn: single foetus (YES/NO); sex; birth-weight (grams); discharged from hospital with mother (YES/NO); APGAR test, separation from the mother during hospital stay (YES/NO); breast-fed during first hours after birth (YES/NO).Regarding breast-feeding: intention to breast-feed (only mother’s milk/only formula/both/I don’t know); received support for breast-feeding during pregnancy (YES/NO); received support for breast-feeding in the hospital (assessment of the attention received in the hospital regarding breast-feeding using the BFHI test); family support measured using the Apgar family test [34]; if breast-feeding took place in the first 30 min.; self-efficacy in breast-feeding measured using the Breastfeeding Self-Efficacy Scale-Short Form (BSES-SF) (test validated in Spain with a global score of 0 to 100); cracks or mastitis in the first 8 days; schedule limitation of feedings.

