## Background

### Feeding newborns: The benefits of breast-feeding

Breast-feeding is the natural way to feed newborns, and human milk is the best-adapted food for their nutritional needs. Breast-feeding (BF) is considered the most adequate way to feed newborns as it provides all of the nutrients that they need to grow and develop in optimal conditions [1]. The World Health Organization (WHO) defines three types of breast-feeding [2]: exclusive breast feeding (EBF), when the infants receive only breast milk, accepting the use of rehydration salts, drops, syrups, vitamins, minerals or medicines; predominant breast-feeding (PBF), when water or water-based liquids and/or fruit juices are added to that included in EBF; and complementary feeding (CF), when any solid or liquid foods, including formula and non-human milk, are added.

BF presents various advantages for newborns, their families and the society in general, taking into account not only the health benefits, but also those that affect social, economic and environmental areas. The short-term benefits for newborns include a better nutritional and immunological state, better intestinal function, and a better establishment of attachment and increased psychological wellbeing [3, 4]. On the long-term, it decreases the risk of diabetes mellitus, obesity, heart disease in adults, certain allergy and inflammatory diseases, and it influences neurocognitive development [5–10]. For mothers, on the short-term it favours uterine involution, weight loss, decreased risk of uterine haemorrhaging, anaemia, hypertension and post-partum depression. On the long-term it acts as a protective factor against the risk of osteoporosis and breast and ovary cancer [4].

Among the social, economic and environmental benefits, BF incurs less costs both for families as well as for health systems while it also decreases the amount of residues and consumption of energy [11].

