### Prevalence of breast-feeding in developed countries: Associated factors

In spite of the broad dissemination of recommendations to promote EBF and its benefits, only 35% of newborns around the world receive EBF after the first three or four months of life [15]. The rates are much lower than those set out by the WHO in European countries, and specifically, in Spain the rates are similar to the rest of the developed countries, with 24.72% EBF at six months, and slightly lower in the Region of Madrid (23.54%) [16].

In Spain the average length of breastfeeding is around 3–5 months. The greater number of abandonments of EBF takes place during the first 4 weeks, (sometimes up to one third of cases) and between the 3rd and 4th months of life, which coincides with the imminent return of the mother to work [17–20].

According to the results of an observational study in Spain the factors that influence the continuity of EBF up to six months are diverse: lack of confidence to breast-feed, pain, suction problems, cracks, infections, ingurgitation, mastitis, baby crying, type of birth, execution of early skin to skin contact, bad experience with prior breast-feeding, comments by family members and/or friends, aspects related with going back to work, and the socio-economic and education level of the mother [21, 22]. Other authors point out the possible effect that the model of the breast-feeding mothers’ mothers, women that lived during periods of setbacks regarding the prevalence of breast-feeding, many of whom most likely did not breast-feed, could have on the breast-feeding mother’s [14].

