## Methods/design

### Objectives

The primary objective of this study is to evaluate the effectiveness of an educational group intervention in primary healthcare, compared to habitual practice (usual care) in increasing the proportion of mother-child pairs that use EBF up to six months of age.

The secondary objectives are:To compare the effectiveness of an educational group intervention in primary healthcare with usual care to increase the proportion of mother-child pairs that use PBF up to six months of age.To describe women’s adherence and degree of satisfaction with the educational group intervention.To describe the reasons for abandonment of breast-feeding in both study groups. To describe the reasons of breastfeeding abandonment in both study groups.To explore the predictive factors of maintenance EBF at six months of age.

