4. Analysis of secondary effectiveness. To evaluate the effect of the educational group intervention on the duration of the different types of breast-feeding, an analysis of survival will be done, making the comparison between the two groups using the log-rank test. The control of the possible confounding variable will be done with the construction of different Cox regression models. The proportion of women that attend at least 85% of the planned sessions will be calculated to study the degree of adherence. The women’s satisfaction with the educational group intervention will be measured with a Likert-type scale.

All *p*-values below 0.05 will be considered as statistically significant for all cases.

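### The six-month feeding outcome has no level for infants no longer breastfed, and a secondary aim of raising PBF, analysed as its own level, pulls against the primary aim of raising EBF

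*Protocol article*

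**What the plan says.** The Background of the protocol article (Feeding newborns: The benefits of breast-feeding) sets the vocabulary: "The World Health Organization (WHO) defines three types of breast-feeding". They are:

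- "exclusive breast feeding (EBF), when the infants receive only breast milk", with allowances such as vitamins and medicines;
- "predominant breast-feeding (PBF), when water or water-based liquids and/or fruit juices are added to that included in EBF";
- "complementary feeding (CF), when any solid or liquid foods, including formula and non-human milk, are added".

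The Outcome variables section turns these into one secondary outcome, "Type of feeding at six months (categorical: EBF, PBF, CF". Table 1 lists the same three states, and no other feeding state, at every visit from 1 to 6.

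The primary objective is to raise the proportion on EBF. The first secondary objective compares the intervention "with usual care to increase the proportion of mother-child pairs that use PBF up to six months of age".

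Item 4 of the Statistical analysis plans log-rank tests and Cox models for "the duration of the different types of breast-feeding". The only duration defined under Outcome variables is that of EBF, from birth to the date EBF was abandoned.

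**The concern.** Two features of the secondary outcomes do not fit the article's own definitions.

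First, CF is introduced as a type of breast-feeding to which other foods are added, so an infant fed on formula alone meets none of the three definitions. The article expects such infants: it collects reasons for giving up breast-feeding as an outcome, and its baseline item on feeding intention separates formula alone from mixed feeding. The outcome does not make that separation.

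Second, EBF and PBF are disjoint, yet the trial aims to increase both. If PBF is compared as its own level, the better the intervention is at keeping would-be PBF pairs on EBF, the worse it looks on the first secondary objective.

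What is at stake is the meaning of the secondary effectiveness comparison, and whether durations other than that of EBF can be calculated from the variables the article defines.

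**Working it through.** **1. The plan's own figure.** The only relevant calculation in the article is the sample size, reproduced here to fix the planned effect and to show that this point leaves it alone. Inputs (Sample size section): control EBF 24%, gain of 15 points to 39%, type I error 5% (taken as two-sided), power 80%, intra-class correlation 0.01, 30 pairs per centre, 10% loss.

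- Two proportions, pooled variance under the null: n = [1.96·√(2 × 0.315 × 0.685) + 0.8416·√(0.24 × 0.76 + 0.39 × 0.61)]² / 0.15² = 149.4, so 150 per arm.
- Design effect: 1 + 29 × 0.01 = 1.29; 150 × 1.29 = 193.5, so 194.
- Loss: 194 / 0.9 = 215.6, so 216 per arm and 432 in total.

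All the stated figures reproduce. The primary outcome is EBF yes or no, and a weaned infant is plainly not on EBF, so nothing below changes them.

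**2. Which level fits which infant**, by the Background definitions:

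| Feeding at six months | Level |
|---|---|
| Breast milk only | EBF |
| Breast milk plus water or juice | PBF |
| Breast milk plus food or formula | CF |
| No breast milk | none |

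**3. Direction of the PBF outcome.** All pairs enter on EBF, so the comparison is between arms: where a pair stands at six months against where it would have stood under usual care.

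- On EBF instead of PBF: primary +1, PBF −1.
- On EBF instead of CF or no breast milk: primary +1, PBF 0.
- On PBF instead of CF or no breast milk: primary 0, PBF +1.
- On PBF instead of EBF: primary −1, PBF +1.

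A fall in PBF can therefore be a benefit, and a rise can be a benefit or a harm.

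**4. Illustration of size.** The article gives no PBF rate. Assume control PBF p of 5% to 20%, let a share f of the 15-point EBF gain come from would-be PBF pairs, and let no other pairs change level. Then the PBF change is −min(p, 15f), and the change in EBF or PBF combined is 15 − min(p, 15f). Changes in points, PBF alone / EBF or PBF:

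| Control PBF | f = 0 | f = 0.25 | f = 0.5 | f = 1 |
|---|---|---|---|---|
| 5% | 0 / +15 | −3.75 / +11.25 | −5 / +10 | −5 / +10 |
| 10% | 0 / +15 | −3.75 / +11.25 | −7.5 / +7.5 | −10 / +5 |
| 15% | 0 / +15 | −3.75 / +11.25 | −7.5 / +7.5 | −15 / 0 |
| 20% | 0 / +15 | −3.75 / +11.25 | −7.5 / +7.5 | −15 / 0 |

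In every cell EBF rises by the planned 15 points. PBF alone never rises, and the combined proportion never falls.

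**5. Durations.** Item 4 speaks of several types of breast-feeding. Outcome variables supplies one formula and one stop date, both for EBF. No listed variable dates the end of PBF or of all breast-feeding.

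**The case against.** The strongest reply is that the practical loss is small, and much of it stands.

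- A reader might infer that weaned infants will have missing data. The article does not support that. The CF definition mentions formula, and with three levels on offer CF is the natural residual. The likely result is a mixed category, not a gap.
- A reader might infer that stopping breast-feeding goes unrecorded and that its duration cannot be obtained. Table 1 asks for reasons for abandonment at each visit, so cessation should come to light and could be placed within about a month. An article need not show every eCRF field either. What remains is that item 4 announces several durations and the stated variables define one.
- PBF could be meant cumulatively, as at least predominant breast-feeding, and the conflict then vanishes. That reading is sensible, but the article does not state it, and its outcome list keeps EBF and PBF as separate levels.
- A reader might conclude that the secondary comparison is beyond rescue. It is not: EBF and PBF are recorded separately, so their sum can be derived from data already planned.
- A reader might take "In Spain the average length of breastfeeding is around 3–5 months" to mean that a large, known share of the sample will be weaned by six months. That sentence describes Spain in general, whereas the trial enrols pairs still on EBF at up to four weeks, after some of the early abandonment has already occurred. The share in this trial is not given.

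**Conclusion.** The point holds, for secondary outcomes only. As written, the outcome list gives an infant no longer breastfed no level of its own and probably merges it with partly breastfed infants under CF. The PBF objective, analysed as its own level, has a sign that indicates neither benefit nor harm. The planned survival analyses cover more durations than the article defines, with cessation captured only indirectly.

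The size cannot be fixed from the article, which gives neither a PBF rate nor the share weaned by six months. The range of 0 to −15 points for PBF rests on the assumed control rate of 5% to 20% and the simple allocation used; zero lies within it. The contradiction in direction rests only on the Background definitions and the two objectives. The primary outcome, its analysis and the 432 pairs are untouched.

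**What to change.** 1. Restate the first secondary endpoint as the proportion on EBF or PBF (at least predominant breast-feeding) at six months, and report the separate levels descriptively.
2. Add a no-breast-milk level to feeding type at every visit, with the date on which all breast-feeding stopped, and state that CF means breast milk plus other food or formula.
3. Define each duration that item 4 will analyse: EBF as now, at least predominant breast-feeding until the first food or formula, and any breast-feeding until the date all breast-feeding stopped.

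The cost is one eCRF response option, one date and some wording, with no extra visits and no change to the sample size. The first change needs no new data. The stopping date should be collected prospectively, because it would be hard to recover reliably afterwards.

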**Methods:**

This study involves a community-based cluster randomised trial conducted at Primary Healthcare Centres in the Community of Madrid (Spain). The project aims to evaluate the effectiveness of an educational group intervention performed by primary healthcare professionals in increasing the proportion of mother-infant pairs using exclusive breastfeeding at six months compared to routine practice.

The number of patients required will be 432 (216 in each arm). All mother-infant pairs using exclusive breastfeeding that seek care or information at healthcare centres will be included, as long as the infant is not older than four weeks, and the mother has used exclusive breastfeeding in the last 24 h and who gives consent to participate.

The main response variable is mother-infant pairs using exclusive breast-feeding at six months.

Main effectiveness will be analysed by comparing the proportion of mother-infant pairs using exclusive breast-feeding at six months between the intervention group and the control group. All statistical tests will be performed with intention-to-treat. The estimation will be adjusted using an explanatory logistic regression model. A survival analysis will be used to compare the two groups using the log-rank test to assess the effect of the intervention on the duration of breastfeeding. The control of potential confounding variables will be performed through the construction of Cox regression models.

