#### Inclusion criteria

Professionals of the randomization unit (CS):
Minimum of 2 years working as a professional in PHC.Have no intention of transferring during the study period.Provide healthcare to the infant population within their daily healthcare workload.Sign the researcher agreement.

Mother-infant dyad:
Mothers of full-term newborns and that use EBF ≥ 18 years of age at the selection visitFull-term newborns (≥ 37 weeks of gestation), with a birth weight > 2.5 kg and with the newborn’s age ≤ 4 weeks.

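### EBF duration is timed from birth with no entry time stated, although pairs enrol while still on EBF at any age up to 4 weeks; curves from birth read too high, and the arm comparison is biased if enrolment age differs by arm

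*Protocol article*

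**What the plan says.** Under Outcome variables, the protocol article defines the secondary duration outcome as "Duration of EBF (days) = (Date of abandonment EBF – Date of birth of infant". The time origin is therefore birth. Statistical analysis, item 4, states "an analysis of survival will be done, making the comparison between the two groups using the log-rank test", and adds: "The control of the possible confounding variable will be done with the construction of different Cox regression models". Neither sentence says when a pair joins the risk set.

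Eligibility depends on breast-feeding status at enrolment. The Inclusion criteria require a mother using EBF and a newborn "with the newborn’s age ≤ 4 weeks". The Abstract (Methods) adds that "the mother has used exclusive breastfeeding in the last 24 h".

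On the timing of stopping, the Background section on prevalence says: "The greater number of abandonments of EBF takes place during the first 4 weeks, (sometimes up to one third of cases".

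On recruitment, the sections Randomisation, Masking and Intervention together say that centres are allocated first and pairs selected consecutively afterwards. The intervention cannot be masked, and the professionals who deliver it also recruit and collect the data.

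The prognostic list for the infant begins "For the newborn: single foetus (YES/NO); sex; birth-weight (grams); discharged from hospital with mother (YES/NO" and goes on to Apgar score, separation from the mother and early feeding. Infant age at enrolment is not in it.

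**The concern.** This is left truncation. A pair enrolled at day 20 could not have been in the study had it stopped EBF on day 10. If that pair is counted at risk from day 0, the risk sets of the first four weeks hold pairs that could not have had an event. By the document's own account, most stopping happens in that window.

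Two consequences need to be kept apart:

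- **Description.** A Kaplan-Meier curve or median from birth, read as time from starting EBF, is too high in both arms.
- **Comparison.** If one arm enrols infants at older ages, that arm shows fewer early events and longer survival with no effect of the intervention. The primary proportion at six months is exposed in the same way, because later entrants have already passed through part of the early drop-off.

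**Working it through.** **Plan's own figures.** The document gives no figure for duration. Its sample size reproduces: 24% v 39%, two-sided 5%, 80% power, no continuity correction gives 150 per arm; 150 × 1.29 = 193.5, so 194; 194/0.9 = 215.6, so 216. The simulations below use 194 pairs per arm.

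**Inputs.** From the document: 24% on EBF at six months, and up to one third stopping in the first 4 weeks. Assumed: a constant stopping rate within days 0–28 and another within days 28–180; S(28), the proportion still on EBF at day 28, of 2/3, 0.80 or 0.90; and the enrolment ages, which the document does not give.

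**Step 1: size of the overstatement.** Let s = S(28), with enrolment age E uniform over 0–28 days.

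- Late rate: h2 = ln(s/0.24)/152.
- True median from birth: 28 + ln(s/0.5)/h2.
- Apparent survival at day 28 with everyone at risk from day 0 (mean of S(28)/S(E)): A = (1 − s)/(−ln s).
- Apparent median: 28 + ln(A/0.5)/h2.

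| Stop by day 28 | h2 | True median | A | Apparent median |
|---|---|---|---|---|
| 33% | 1.0217/152 = 0.00672 | 28 + 0.2877/0.00672 = 71 | 0.3333/0.4055 = 0.822 (true 0.667) | 28 + 0.4973/0.00672 = 102 |
| 20% | 1.2040/152 = 0.00792 | 28 + 0.4700/0.00792 = 87 | 0.2/0.2231 = 0.896 (true 0.80) | 28 + 0.5837/0.00792 = 102 |
| 10% | 1.3218/152 = 0.00870 | 28 + 0.5878/0.00870 = 96 | 0.1/0.1054 = 0.949 (true 0.90) | 28 + 0.6409/0.00870 = 102 |

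Taking six months as 182 days moves these medians by about one day (103 against 97 in the last row).

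**Step 2: comparison between arms under no effect.** Stopping times were drawn conditional on EBF at the enrolment age. The log-rank test was run with all pairs at risk from birth, and again with each pair at risk from enrolment. There were 1,000 to 2,000 runs per scenario, and clustering was ignored.

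| Stop by day 28 | Mean entry age | At risk from birth | Delayed entry |
|---|---|---|---|
| any of the three | equal | rejects about 5%, HR about 1.00 | about 5% |
| 33% | 10 v 17 days | about 20%, HR 0.87 | about 5% |
| 20% | 10 v 17 days | 8 to 11%, HR 0.93 | about 5% |
| 10% | 10 v 17 days | about 6%, HR 0.96 | about 5% |

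The 8 to 11% is the spread over repeat runs with different shapes of the entry-age distribution around nearly the same means.

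**Step 3: the primary proportion under no effect.** For a pair entering at age a (up to 28 days), the proportion on EBF at six months is 0.24/S(a) = 0.24 × exp(h1 × a), with h1 = −ln(s)/28.

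- 33% stopping, h1 = 0.01448: 0.24 × exp(0.1448) = 27.7% at day 10; 0.24 × exp(0.2462) = 30.7% at day 17. Difference 3.0 points.
- 10% stopping, h1 = 0.00376: 0.24 × exp(0.0376) = 24.9% at day 10; 0.24 × exp(0.0640) = 25.6% at day 17. Difference 0.7 points.

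**The case against.** The strongest reply has five parts.

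1. **Each pair's duration is correct.** Date of stopping minus date of birth is right for every enrolled pair, and the study population is pairs on EBF who present in the first month, not all infants who start EBF. This stands. The overstatement concerns only how a curve or median from birth is read.
2. **No age gap, no bias between arms.** Both arms share the same age limit, the same Visit 1 window and consecutive sampling. This stands: with equal ages the type I error is about 5%. A reader might infer that the plan favours the intervention arm, but the document gives no enrolment ages by arm, so neither a gap nor its direction can be claimed. Unmasked recruitment after allocation makes a gap possible, and consecutive sampling does not equalise age.
3. **One third is an upper limit.** This stands, and it may also mean one third of those who stop, which is 0.76/3, or about 25% of pairs. At 10% the 7-day gap leaves the test close to nominal. The simulations also ignore clustering, which the plan says it will handle, so the rejection rates are not those of the planned test.
4. **Baseline checks might pick it up.** Statistical analysis, item 2, compares baseline characteristics as well as prognostic factors and adjusts for imbalance. Infant age is not excluded, so it would be too strong to say that the plan could not detect a gap. But the age is not named, and adjustment there depends on an observed imbalance.
5. **Delayed entry may be specified elsewhere.** Birth as the time scale is compatible with it, and a fuller document could add it. The article, however, fixes the origin and the tests without it, and read as written they treat every pair as at risk from birth.

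**Conclusion.** The point holds in limited form. As written, the duration analysis counts event-free time before enrolment as time at risk, in the weeks that the document identifies as having the most stopping.

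The apparent median exceeds the median from birth by about 31 days (102 − 71) at the document's upper limit, and by about 6 days (102 − 96) at 10% early stopping, with enrolment spread evenly over 0–28 days. The comparison between arms is distorted only under an age gap that must be assumed; at 7 days the size runs from clear (about 20% rejections) to negligible (about 6%).

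Duration is secondary. For the primary proportion, the same assumed gap moves the difference by 0.7 to 3.0 points against the planned 15. A reader might infer that the primary result is invalid; nothing in the document supports that. The change is still worth making, because it needs only dates the trial requires anyway.

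**What to change.** - Keep infant age as the time scale, and state that each pair enters the risk set at its age at enrolment. Apply this to the log-rank test, the Cox models and the Kaplan-Meier curves (left-truncated versions).
- Prespecify infant age at enrolment as a covariate in the primary logistic model, whether or not an imbalance is seen. Delayed entry in the survival analysis does not correct the six-month proportion, so this is a separate step.
- Add infant age at enrolment to the prognostic list and report it by arm.
- Do not replace this with curves conditional on EBF at day 28. They drop enrolled pairs who stop between enrolment and day 28, which conflicts with the intention-to-treat analysis.

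**Cost.** A change of analysis wording. Birth date is needed for the duration formula and consent is taken at Visit 1, so no new visit or measurement is required. The early part of the curves will rest on fewer pairs, and the reported durations will look less favourable.
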